**Intervention**

**Intervention and data collection**

The project will utilise a simple application (app)set up on each participant’s or parent/guardian’s mobile smartphone, tablet, or other device that will allow video capture and transmission of ICS inhaler administration. Before the study intervention period is initiated in a given subject, the participant and/or parents/guardians will be trained in use of the video DOT application and how to upload the videos to a web-based repository. As a general rule, it would be expected that young people greater than 12 years of age will record and upload the video themselves, while parent/guardian assistance will be needed for younger children. All mobile devices will be tested after installation to make sure the Dropbox®([https://www.**dropbox**.com](https://www.dropbox.com))repository connection is active and ready to use.

Usual asthma care for the participant will be adopted throughout the study. Regarding the inhaler use, children aged 5 years or older may administer the medication themselves while a parent/guardian will be responsible for inhaler administration in patients 2 up to 5 years of age. However, parent/guardian administration will be allowed if that is usual asthma care in any age child.

Patients who are enrolled in the study will be randomised into two groups (I-med or D-med) as previously described. Participants or parents/guardians of participants will be asked to capture a DOT video twice daily (morning and evening) on their mobile devices of ICS use by the patient. It will be requested that morning videos occur before 9am on school days and before 11am on weekends and holidays, and evening videos occur between the evening meal and bedtime. In the I-med group, participants will be asked to upload daily video recordings via the internet to a repository for a 6 week period at the start of the study. Participants in the D-med group will be free from DOT for the first 6 weeks of the study and will be asked to carry out their usual therapy management. After that, DOT as described above will be applied for the next 6 weeks.

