Researchers will evaluate the DOT uploads daily through their password protected access to the video repository. Children and their parent/guardians also will have access to their own videos within the password protected repository. A research team member will follow up with parents/guardians and/or a participant by telephone if two consecutive days of video uploads are missed. The asthma clinical team (consultant/nurse) providing the usual asthma clinical management will be notified about children identified with poor inhaler technique.

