**At study end (both groups)**

- GP prescribing records for the 12 months leading up to, and during the study time period
- Community pharmacy dispensing records for the 12 months leading up to, and during the study time period

Clinician assessment of participant asthma severity will be defined according to accepted guidelines and asthma control will be categorized as uncontrolled, partially controlled, or controlled (BMT/SIGN 2012). Data regarding the medication profile will include any respiratory or allergy drugs added or removed, existing drug dosage changes, and drugs initiated for respiratory infections.

Patient inhaler technique will be evaluated by reviewing each video from the first 2 days of the intervention period and then a sample (at least one weekly) of the videos that have been uploaded to the repository application. The presence/absence of every required video will be documented.

Inhaler technique will be assessed and categorized on a three-point scale as effective, partially effective or poor (Patterson *et al.*, 2005). Inhaler technique evaluation will be based on criteria relevant to the child’s inhaler manufacturer administration directions, such as removal of cover, priming of device, vigorous shaking before each actuation, respiratory expiration before actuation, and holding of breath after inspiration. Effective technique will be recorded when the participant meets all relevant criteria. Partially effective technique will be recorded when errors in technique are observed but it is thought that the participant would receive some medication. Poor inhaler technique will be recorded when critical errors in technique occur such that it is considered unlikely that any medication would be inhaled (Patterson *et al.*, 2005; Melani *et al.*, 2011).

Adherence will be calculated based on total number of videos submitted during the 6 week intervention divided by the number of days during which DOT monitoring has occurred.

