**Feedback questionnaires**

Parents/guardians will be asked to respond to feedback questionnaire to provide their views and experience about the use of the technology at the end of intervention (6 weeks) or in cases where a participant is unable to complete the study. Feedback questionnaires will be sent to each participant by the post and each participant will be contacted by telephone for a reminder if the questionnaire is not returned within a two week period. This feedback will be used to document participant’s experience or record any difficulties with using the mobile DOT approach in the study. Moreover, participants feedback will help us make improvements to the approach for the future. Two feedback questionnaires have been prepared by the research team: one for participants who completed the 6 week period of using mobile DOT (Appendix 20) and the second for participants who consented to take part but did not upload videos or who uploaded videos for a shorter period that the 6 weeks requested (Appendix 21).

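### The video adherence ratio divides by days although two videos a day are required, so it tops out at 2, and its undefined count of monitored days may leave early stopping unpenalised

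*Protocol*

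**What the plan says.** Under Intervention and data collection, families are "asked to capture a DOT video twice daily (morning and evening) on their mobile devices of ICS use by the patient". The length is set in the same section; for the immediate group, "participants will be asked to upload daily video recordings via the internet to a repository for a 6 week period". The delayed group does the same for 6 weeks after its DOT-free interval.

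Under Outcome measurements, At study end (both groups), video adherence is the "total number of videos submitted during the 6 week intervention divided by the number of days during which DOT monitoring has occurred". The same section states that "The presence/absence of every required video will be documented".

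Two other places bear on what a monitored day is. Under Intervention and data collection, "Researchers will evaluate the DOT uploads daily through their password protected access to the video repository", and the team telephones the family after two consecutive days without uploads. Feedback questionnaires provides a separate form for participants who consented but "did not upload videos or who uploaded videos for a shorter period that the 6 weeks requested".

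Outcomes measure places feasibility, practicality and persistence in the first primary outcome area, assessed partly by monitoring adherence. Data analysis lists video submissions as one source of adherence, alongside GP records, dispensing records and MARS scores.

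**The concern.** The numerator counts videos, requested twice a day, and the denominator counts days. The ratio is therefore not a proportion of what was asked for, and the protocol does not say which value means full adherence. The Background gives its comparison figures as percentages: about 50% for inhaled steroids in children, and 95%, 97.5% and 93.3% in earlier observed-therapy studies. A mean ratio of 1.0 set beside these would look like complete adherence when half the videos were missing.

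The denominator is also not pinned down. The numerator covers the 6-week intervention, but the denominator is a count of days on which monitoring took place. The protocol does not say whether days after a family stops uploading belong to that count. Persistence is part of the primary outcome area and early stoppers are expected, so the answer decides whether the measure can show loss of persistence at all.

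**Working it through.** The protocol prints no adherence value, so there is no figure to reproduce. The check applies the stated formula to simple upload patterns.

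**Inputs**
- Videos requested per day: 2 (Intervention and data collection).
- Length of the DOT period: 6 weeks = 42 days (same section).
- Videos required: 2 × 42 = 84.
- Formula: videos submitted ÷ days monitored (At study end).

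**Step 1: scale.** A child who sends every video scores 84/42 = 2.0. A child who sends one a day throughout scores 42/42 = 1.0, against 42/84 = 50% of the videos required. These values are the same whether days monitored means all 42 days, days until uploads stop, or days with at least one upload.

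**Step 2: meaning of the denominator.** The two columns in the middle apply the formula under different readings; the last gives the share of required videos.

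| Upload pattern | Videos | ÷ 42 days | ÷ days until uploads stop | Videos ÷ 84 |
|---|---|---|---|---|
| Two a day, 42 days | 84 | 2.0 | 2.0 | 100% |
| 63 videos over 42 days | 63 | 1.5 | 1.5 | 75% |
| One a day, 42 days | 42 | 1.0 | 1.0 | 50% |
| Two a day, stops after day 14 | 28 | 0.67 | 28/14 = 2.0 | 33.3% |
| Two a day, stops after day 7 | 14 | 0.33 | 14/7 = 2.0 | 16.7% |
| One a day, stops after day 14 | 14 | 0.33 | 14/14 = 1.0 | 16.7% |
| Never uploads | 0 | 0 | 0/0, undefined | 0% |

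Counting only days with at least one upload gives the same values as the days-until-stopping column for these patterns. It adds one more distortion: a child who sends two videos on alternate days throughout scores 42/21 = 2.0 while supplying 42/84 = 50% of the videos.

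**Step 3: ranking.** With a denominator that shrinks when uploads stop, the day-7 stopper (2.0) ties with the full persister (2.0) and outranks the child with 63 videos over 42 days (1.5). With 42 days for everyone, the stopper (0.33) ranks below both.

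**The case against.** The strongest reply is that a 42-day denominator fits the text at least as well. Researchers check the repository daily and telephone after two missed days, so monitoring continues when nothing is uploaded, and absent videos are logged as data. On that reading the ratio is exactly twice videos/84. Rankings, t-tests, rank tests and regression p-values do not change, and a ratio read as videos per day is correctly labelled. The protocol states no percentage and no threshold. This stands as far as it goes: the protocol does not settle the reading, and on the 42-day reading the fault is one of scale only. It does not remove the ambiguity, because the denominator is worded as a realised count rather than as the planned 6 weeks.

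A reader might infer that early stoppers score higher than children who persist. The formula does not support that in general. It requires a shrinking denominator and a persister with a lower daily rate, and no stopper can exceed a full persister because both are capped at 2.0. A reader might also infer that never-uploaders leave the analysis. The protocol does not say so, and 0/0 arises only on the shrinking reading. Nor does the protocol make this ratio the sole outcome of the regression on non-adherence, since Data analysis draws adherence from several sources.

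Finally, scoring every randomised child out of 84 would give 0% to a delayed-group child who withdrew before starting DOT. That objection is right and limits the fix.

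**Conclusion.** The mismatch of units is certain on every reading: the scale runs from 0 to 2, and half of the required videos gives 1.0. Calling these values 200% and 100% assumes that the ratio is reported as a proportion. The protocol does not say that it will be, though its own comparison figures invite it.

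The effect on persistence is conditional. If days after uploads stop are left out, a child who supplied 16.7% of the required videos (two a day for 7 days) can score the maximum, and non-persistence is hidden in a measure that feeds the first primary outcome area. If all 42 days count, the same child scores 0.33 and only the reported level needs correcting. The claim that feasibility is overstated therefore holds on the first reading, or if the ratio is read as a percentage, and not otherwise. Because the protocol fixes this formula itself, it should be corrected before the data are analysed.

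**What to change.** Replace the sentence defining video adherence. For every child who reaches the start of the DOT period, define it as required videos submitted, counting at most one morning and one evening video per day, divided by 84 (2 × 42 scheduled days) and expressed as a percentage. State that days after the last upload count as missed and that a child who starts the period but never uploads scores 0%. Report the duration of uploading, from the start of the DOT period to the last upload, separately as persistence.

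The cost is one or two sentences. No new data are needed, because the log of present and absent videos already supplies both numerator and denominator. The small downside is a lower reported adherence figure.

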**Feedback questionnaires**

Parents/guardians will be asked to respond to feedback questionnaire to provide their views and experience about the use of the technology at the end of intervention (6 weeks) or in cases where a participant is unable to complete the study. Feedback questionnaires will be sent to each participant by the post and each participant will be contacted by telephone for a reminder if the questionnaire is not returned within a two week period. This feedback will be used to document participant’s experience or record any difficulties with using the mobile DOT approach in the study. Moreover, participants feedback will help us make improvements to the approach for the future. Two feedback questionnaires have been prepared by the research team: one for participants who completed the 6 week period of using mobile DOT (Appendix 20) and the second for participants who consented to take part but did not upload videos or who uploaded videos for a shorter period that the 6 weeks requested (Appendix 21).

**Data protection**

All participants’ data will be coded and entered into a database, using a unique study ID number, on the University’s firewalled server. The same approach of using study IDs will be applied to the video repository. Access to the custom designed, study specific repository, to be created in DropBox® will be password protected such that only researchers can access all files within the system, while study participants will only be able to access files which they have loaded themselves (again password protected). Hard copies of consent forms will be stored in a locked cabinet within the Clinical and Practice Research Unit in the School of Pharmacy, Queen’s University Belfast.

**Outcomes measure**

The primary outcome measures in this pilot study concern two areas. Firstly, the feasibility, practicality, and persistence of using a mobile DOT approach in the management of asthma in children and young people will be assessed by evaluation of ICS inhaler technique and monitoring inhaler use adherence. Secondly, asthma control associated with the mobile DOT approach will be assessed with clinical (including number of patients who progress to controlled category) and laboratory disease assessment, participant-reported medication adherence, and quality of life measurements (PAQOLQ/PACQOLQ and ACT/C-ACT).

Secondary outcome measures for the study include any impact of mobile DOT on participants’ inhaler technique and adherence. These two aspects of asthma management will be assessed by comparisons between intervention groups and within groups during, and across, phases of the study. Participant and parent/guardian factors that influence the impact of the DOT method on inhaler use and adherence also will be determined.

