**(c) Sample size calculation**

The variability in quality of life (QOL) score changes in a similar population was reported in a pilot study to be 1.3 units (Young *et al.*, 2001). To have an 80% power to detect a statistically significant (P<0.05; two-tailed Student t-test) difference for effect of the intervention between groups of 1 QOL unit would require 36 children per group.

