**At 6 weeks**

- Clinician assessment of asthma control
- Asthma medication profile and any changes made at clinic visit
- Number of asthma ‘attacks’, oral corticosteroids courses, and emergency attendances since baseline visit.
- Spirometry measurement; FeNO.
- Self-reported MARS
- PAQOLQ/PACQOLQ and ACT/C-ACT
- ICS inhaler technique

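### Several asthma-control measures are primary with no ranking or time point, while the trial is sized on one QOL comparison at 5%; testing five or six gives roughly an 18% to 26.5% false-positive chance

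*Protocol*

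**What the plan says.** The Outcomes measure section of the protocol opens: "The primary outcome measures in this pilot study concern two areas". The first area is whether the mobile DOT approach is feasible, practical and kept up; it "will be assessed by evaluation of ICS inhaler technique and monitoring inhaler use adherence". The second is asthma control, assessed by clinical evaluation (including how many children move into the controlled category) and by "laboratory disease assessment, participant-reported medication adherence, and quality of life measurements (PAQOLQ/PACQOLQ and ACT/C-ACT"). No measure is ranked above another and no visit is named as primary.

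The next paragraph reads: "Secondary outcome measures for the study include any impact of mobile DOT on participants’ inhaler technique and adherence". It places the between-group and within-group comparisons of these two aspects in the secondary tier.

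The Sample size calculation section takes one outcome, a QOL score, with an SD of change of 1.3 units and a between-group difference of 1 unit. It asks for 80% power for a result that is "statistically significant (P<0.05; two-tailed Student t-test"), and arrives at 36 children per group.

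The visit lists put "Spirometry measurement; FeNO" side by side at weeks 6, 12 and 18 in both groups, and again at week 24 in the delayed group. The Data analysis section applies a t-test or Mann-Whitney test to group differences and paired t-tests within groups, and says that nominal data are handled descriptively.

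**The concern.** A 5% error rate and a stated power belong to a particular test. Here they were worked out for one QOL comparison, but the outcome list gives the same primary rank to several other measures of asthma control. With no ranking and no primary visit, the choice of which result to present as the primary finding stays open until the data have been seen. If DOT does nothing, the chance that at least one primary measure crosses 0.05 is then well above 5%, and a reader of the results could not tell a planned test from a selected one.

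The visit matters as much as the measure. The delayed group starts DOT at week 6 and has finished it by week 12. Week 6 is therefore the only visit at which a group that has had DOT is compared with one that has not. Later visits compare two groups that have both had it.

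**Working it through.** **1. The plan's own figure.** Inputs from the Sample size calculation section: difference 1, SD 1.3, two-sided 0.05, power 80%.

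- Normal formula: n = 2 × (1.960 + 0.842)² × 1.3² / 1² = 26.5, so 27 per group. The exact t calculation gives 27.5, so 28.
- The stated 36 is not reproduced. At 90% power the normal formula gives 2 × (1.960 + 1.282)² × 1.69 = 35.5, so 36.
- At 36 per group the recomputed power is 90.4% (normal) or 89.6% (t). The 90% used below is this recomputation; the protocol states 80%. An unstated dropout allowance would also lead to 36, for example 27/(1 − 0.25) = 36. Where the 36 comes from is a separate matter.

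**2. How many primary comparisons?** Taking the laboratory assessment to be spirometry and FeNO, which is an assumption because the Outcomes measure section does not define it:

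| Measure | Compared between groups as a primary outcome? |
|---|---|
| QOL (PAQOLQ/PACQOLQ) | Yes |
| ACT/C-ACT | Yes |
| Self-reported adherence (MARS) | Yes |
| Spirometry | Yes |
| FeNO | Yes |
| Control category | Possibly; descriptive only if treated as nominal |
| Inhaler technique | Primary for feasibility; comparisons are secondary |
| Inhaler-use adherence | As for technique; the delayed group has no videos in weeks 0 to 6 |

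That gives five comparisons, or six with control category. Eight is the count only if every measure is tested as primary.

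**3. Chance of at least one false positive.** Assume one between-group test per measure at 0.05, with no true effect on any of them.

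- Independent tests: 1 − 0.95^k. For k = 5 this is 0.226, for k = 6 it is 0.265, for k = 8 it is 0.337.
- Correlated tests: simulate z_j = √ρ·c + √(1−ρ)·e_j with c and e_j standard normal (500,000 runs), and count runs in which any |z_j| exceeds 1.96.

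| Assumed ρ | 5 tests | 6 tests | 8 tests |
|---|---|---|---|
| 0 | 22.6% | 26.5% | 33.7% |
| 0.3 | 20.8% | 24.2% | 29.9% |
| 0.5 | 18.2% | 20.8% | 25.1% |
| 0.8 | 12.8% | 13.9% | 15.7% |

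The correlations are assumptions; the protocol gives none.

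**4. What adjusting would cost instead.** Splitting 0.05 over six measures gives 0.05/6 = 0.0083 each. At 36 per group the QOL test then has 71% power, against the recomputed 90%, and about 43 per group would be needed for 80%. Over eight measures (0.00625 each) the figures are 67% and about 46 per group.

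**The case against.** The protocol calls the study a pilot, no sentence says that one significant result means success, and a multiplicity rule could sit in a statistical analysis plan that is not at hand. All of that stands, and the lack of such a rule is not the point here. But the protocol itself sets the outcome ranks, powers a hypothesis test, and makes clinical impact part of its principal aim. The mismatch between the primary list and the sample size is therefore in this document.

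It is also fair to object that making QOL the one efficacy primary moves away from the principal aim, which concerns inhaler technique and adherence. QOL is proposed because it is the only outcome with sample-size inputs. A different choice is open to the sponsor but would need its own calculation.

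Three stronger readings are tempting, and the documents do not support them:

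- **Eight primary tests, with a false-positive chance of 25% to 34%.** Technique and inhaler-use adherence are primary only as feasibility measures, video adherence has no concurrent control in weeks 0 to 6, and control category may be descriptive. The 34% needs all eight measures to be tested and independent.
- **Multiplying the measures by the three shared post-baseline visits.** Nothing says that every visit is a primary test. Video adherence belongs to each group's own six-week window and is not a visit measure.
- **A plain contradiction because technique and adherence appear in both tiers.** The first mention is about whether DOT can be carried out, the second about its effect. The wording is unclear, but these are two questions asked of the same data.

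**Conclusion.** The concern holds in a limited form. The stated 5% level and 80% power apply to one QOL comparison, while the protocol gives primary rank to a set of asthma-control measures without order or time point. On the best-supported count of five or six comparisons, the chance of at least one false-positive primary result is about 18% to 26.5% at assumed correlations of 0.5 to 0, and about 13% to 14% at 0.8. Even the lowest of these is about two and a half times the nominal 5%.

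The figures assume one between-group test per measure at 0.05, no true effect on any measure, equal correlation between measures, and spirometry and FeNO counted separately. The direction does not depend on the exact count; the size does. In a study labelled a pilot, with no stated rule that any one result means success, this should be fixed, but it does not invalidate the design.

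**What to change.** In the Outcomes measure section:

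- Name one primary efficacy outcome: the between-group comparison of QOL at week 6, as change from baseline, since the 1.3 SD refers to score changes. State how PAQOLQ (used from age 9) and PACQOLQ are assigned and whether they are combined, because the sample size section names neither.
- Keep one feasibility primary: the proportion of required videos received in each child's own six-week period (two a day for 42 days, so 84), with a confidence interval and no test. The protocol already plans to record the presence or absence of every required video.
- Make control category, ACT/C-ACT, spirometry, FeNO, MARS and technique secondary.
- Word technique and adherence so that their feasibility role and their role as measures of DOT's effect are distinct.

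This costs protocol wording only, with no extra children or visits, and should be settled before outcome data are seen. The downside is that positive results on the other measures become supportive only. The alternative, several primary measures with the 5% split between them, would need about 43 per group for six measures to keep 80% power for QOL.

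### Persistence with mobile DOT is part of a primary outcome, but the only stated video statistic is a pooled 6-week rate whose ambiguous denominator either hides early stopping or rewards it

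*Protocol*

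**What the plan says.** Persistence appears twice as a main question of the study. Objective 1 (Aims and objectives) lists it beside feasibility and practicality. Outcomes measure places it in the first of two primary areas: "the feasibility, practicality, and persistence of using a mobile DOT approach in the management of asthma in children and young people will be assessed". The same sentence says how: "by evaluation of ICS inhaler technique and monitoring inhaler use adherence". No time unit, threshold or summary for persistence is given anywhere.

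The one calculation for video adherence is under At study end (both groups): "total number of videos submitted during the 6 week intervention divided by the number of days during which DOT monitoring has occurred". Intervention and data collection asks for two videos a day, morning and evening, for 6 weeks.

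The section with the formula also states: "The presence/absence of every required video will be documented". Feedback questionnaires provides one form for families who complete 6 weeks of filming. A second form covers those who never upload or who stop early.

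**The concern.** Persistence is about time: whether families keep filming as the weeks pass. The protocol assigns it to adherence monitoring and then gives, for the videos, one pooled figure per child with no time element. A moderate average could come from stable use or from a collapse by week 6, and these point in opposite directions on whether home DOT can be continued or extended.

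The denominator makes this worse. Days of monitoring that occurred may mean the 42 days of the intervention. It may also mean only the days until a child stops, or only the days with an upload. The choice changes both the score and the ranking of children. If it is left open, it can be settled after the uploads have been seen.

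**Working it through.** The plan gives no figure for persistence, so there is none to reproduce. The check applies the stated formula to assumed upload patterns, which are illustrations and not trial data.

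**Inputs from the protocol.** Two videos per day (Intervention and data collection) for 6 weeks: 6 × 7 = 42 days, 2 × 42 = 84 scheduled videos, 14 per week. The formula is total videos ÷ days monitored. It is therefore a rate in videos per day with a maximum of 2.0, not a proportion.

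**Reading 1: the denominator is the fixed 42 days.** Three assumed children each send 54 videos:

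| Pattern | Videos in DOT weeks 1–6 | Total | Total ÷ 42 | Week-6 rate |
|---|---|---|---|---|
| Steady | 9, 9, 9, 9, 9, 9 | 54 | 1.29 | 9/14 = 64% |
| Declining | 14, 13, 11, 8, 5, 3 | 54 | 1.29 | 3/14 = 21% |
| Full for 27 days, then stops | 14, 14, 14, 12, 0, 0 | 54 | 1.29 | 0/14 = 0% |

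All three score 54/42 = 1.29 per day (54/84 = 64% of scheduled videos). The statistic cannot tell them apart.

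**Reading 2: the denominator ends at the last upload.** The child who stops after day 27 scores 54/27 = 2.0. A child who films everything for the full period scores 84/42 = 2.0. Early stopping and perfect use now tie at the maximum.

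A second set of assumed patterns, each with 42 videos, shows that the order can also reverse:

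| Pattern | Total ÷ 42 | Total ÷ days to last upload | Videos by week |
|---|---|---|---|
| 1 per day for 42 days | 1.0 | 42/42 = 1.0 | 7, 7, 7, 7, 7, 7 |
| 2, then 1, then 0 per day, 14 days each | 1.0 | 42/28 = 1.5 | 14, 14, 7, 7, 0, 0 |
| 2 per day for 21 days, then none | 1.0 | 42/21 = 2.0 | 14, 14, 14, 0, 0, 0 |

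The child who stops earliest scores best. In these three patterns, counting only days with an upload gives the same values as counting days to the last upload. Under either of those counts, a child who never uploads has 0/0, which is undefined. Under the fixed count that child scores 0/42 = 0.

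**What the log adds.** In both tables the weekly counts separate the patterns at once, and they come directly from the per-video record the study already keeps.

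**Elsewhere in the protocol.** Data analysis names t-tests, the Mann-Whitney test, chi-squared and Fisher tests, and multiple regression. The paired t-test compares study periods. None of these describes uploads over time within the 6 weeks.

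**The case against.** The strongest reply is that the data are not missing. Each expected video is logged, uploads are checked daily, a call follows two consecutive missed days, and the two feedback forms separate completers from the rest. Data analysis promises descriptive treatment of nominal data and lists monitoring of video submissions as an adherence source. The formula is offered as adherence and is not labelled as persistence. Weekly summaries might also be set out in a statistical analysis plan that is not at hand.

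Much of this stands, and it rules out three stronger readings:

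- **That persistence cannot be reported at all.** It can be derived from the log. The gap is in the definition and the stated calculation.
- **That steady use, decline and early stopping give the same result whatever the denominator.** They tie only with the fixed 42 days. With a denominator that ends at stopping they differ, and the early stopper gains.
- **That the secondary comparison of technique and adherence, by "comparisons between intervention groups and within groups during, and across, phases of the study", cannot be made.** MARS is completed at each visit and technique is rated from at least one video a week, so that comparison does not rest on the 6-week video total alone.

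The reply does not remove the core. The protocol is not simply silent: it says persistence is assessed through adherence monitoring, and it fixes the one video adherence formula. The second feedback form combines children who never started with those who stopped early. It also collects views by post and is not described as a persistence measure. The telephone call is a study procedure. A general promise of description does not say which summary answers a primary question.

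**Conclusion.** The point holds as a badly fixed rule for one component of a primary outcome. Followed as written, the pooled rate hides early stopping (1.29 per day for week-6 rates of 64%, 21% and 0%) or rewards it (2.0 per day for 27 days of filming, equal to full use). In neither case does it show whether filming was kept up.

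The examples assume particular upload patterns. How often such patterns will occur is unknown, so the effect on the group result cannot be sized from the protocol. The conclusion needs only that some families decline or stop early, which the protocol itself anticipates with its second feedback form. The matter is one of definition and analysis, and it can be put right before any uploads are examined.

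**What to change.** Amend At study end (both groups) and Outcomes measure as follows:

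1. **Overall video adherence:** videos received ÷ 84 scheduled (2 per day × 42 days), with days after stopping counted as missed. This gives a proportion and defines the score for children who never upload (0/84 = 0).
2. **Persistence:** from the per-video log, the proportion of the 14 scheduled videos received in each of DOT weeks 1 to 6, counted from each child's own DOT start so that both groups are on the same scale. Add the proportion of children still uploading in week 6 with a 95% CI, and state in advance what counts as still uploading.

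Both parts are needed. The fixed denominator stops early stopping from being rewarded, but only the weekly figures show it. A model for the weekly trend, or a Kaplan-Meier curve for time to last upload, is optional.

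The cost is a few sentences of wording and a short table. No new data, visits or participants are required.
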